### Sample size justification

The sample size requirements for this study are intended to provide adequate power for the analysis of the primary objective.

Simulation methods used data extrapolated from a population of 160 CRT-D patients followed up for 224 ± 130 days (data on file). Overall, 220 episodes occurred over 98 person-years (2.2 per person-year):

• 140 intra-thoracic impedance alerts;

• 34 episodes of atrial arrhythmia >12 hours in a single day;

• 6 additional episodes of atrial arrhythmia >6 hours with ventricular rate >100 beats/min in a single day;

• 40 ICD shocks delivered.

The simulations were run in R Software 2.4.1 according to the following hypotheses: the incidence density used as a null hypothesis was 2.2 per person-year; this rate is expected to decrease by 10% in the study arm; it was assumed that 20% of patients would drop out uniformly over the follow-up period; the target type-I error (α) was 0.05.

A sample size of 100 subjects per group would allow a power of 99.8% (95% confidence interval: 96.0 – 100.0) to detect an incidence rate ratio of 0.90, with a type-I error of 0.05.

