### Objectives

The primary objective of the study is to determine whether patients using the CareLink system display a different rate of unplanned cardiac or device-related in-hospital visits from patients in the standard arm. The endpoints for this objective include all cardiac and device-related clinic visits, i.e. all hospital admissions not involving an overnight stay, when the interval between the decision to admit and the admission is <24 hours. The events anticipated to prompt these visits are: ICD alerts regarding system integrity, atrial and ventricular arrhythmias, decrease in intra-thoracic impedance signifying possible fluid accumulation, and patients' symptoms. These endpoints will be subdivided according to whether the visits are related or not related to episodes of worsening of HF; estimation of their respective rates will constitute a secondary objective of the study.

Additionally, the rate and related costs of total healthcare utilizations (all planned and unplanned hospital admissions involving and not involving an overnight stay) for cardiac or device-related events will be compared between groups. For this objective, hospital visits will be also scrutinized and classified as necessary or unnecessary for the clinical management of the patient. In particular, each visit will be judged necessary if it results from an appropriate and clinically meaningful ICD alert (e.g.: intra-thoracic impedance alert associated with clinically deteriorated HF) and if the clinician was not previously aware of the clinical/ICD condition.

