***AT/AF Burden and Rate Settings***		

*AT/AF Daily Burden Alert Enable – Device **	Off	On

*AT/AF Daily Burden Alert Enable – Monitor **	On	Off

*- Daily AT/AF Alert Burden*	6 hours	6 hours

*Avg. V. Rate During AT/AF Alert Enable – Device ***	Off	On

*Avg. V. Rate During AT/AF Alert Enable – Monitor ***	On	Off

*- Avg. V. Rate During AT/AF*	100 beats/min	100 beats/min

*- Daily Burden for Avg. V. Rate*	6 hours	6 hours

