### Rationale for design

Currently, outpatient follow-up examinations of ICD patients are scheduled at regular 3- to 6-month intervals [8,9]. In the present study, we will compare a standard arm undergoing 4 in-office examinations per year with a remote arm in which 2 of the 4 examinations are replaced by remote interrogations, as previously proposed [16,17].

Acute events, such as ICD shocks, alerts or symptoms that usually prompt the subject to seek urgent attention at the clinic, will be managed via CareLink and telephone follow-up in the remote arm. Indeed, it has been recently shown that a considerable portion of post-shock interrogations do not involve reprogramming of the ICD and may therefore be performed remotely [10,15].

The audible alert feature has been shown to facilitate the early discovery of serious ICD complications [7], and improved alert algorithms have recently been implemented to detect lead failures promptly [6]. Similarly, in view of the high incidence of atrial fibrillation in HF [18] and the consequent increased risk of decompensation, stroke and inappropriate shocks, the advanced ICD capabilities for detecting atrial arrhythmias have the potential to play a growing role in patient monitoring [5]. By providing remote notification and access to details of the occurrence and duration of atrial fibrillation and ventricular response, CareLink will facilitate the management of therapies for rhythm or rate control and the prompt administration of anticoagulants for stroke prevention.

Continuous intra-thoracic impedance monitoring in modern ICD is intended to detect HF decompensation promptly, thereby permitting early therapeutic intervention [4]. Decreased intra-thoracic impedance has been shown to reliably identify acute HF, with low rates of undetected events [19], and to be associated with an increased risk of HF hospitalization [20]. As recently shown [15], a high percentage of episodes may be successfully and promptly managed through CareLink without requiring additional in-hospital visits, by means of remote data review and assessment of symptom status and therapy compliance by phone. Moreover, patients might not hear or respond to the audible impedance alert, as recently reported [21]. Thus, automated telemetric transmission of alerts to the physician may shorten the delay between alert and therapy initiation, further improving the clinical outcome.

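### The planning rate of 2.2 per person-year counts device-detected episodes and is used, without saying so, as a one-to-one stand-in for unplanned hospital visits

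*Protocol article*

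**What the plan says.** Under Objectives, the protocol article sets out to learn whether patients on the remote system "display a different rate of unplanned cardiac or device-related in-hospital visits from patients in the standard arm". The same section lists alerts, arrhythmias, falls in impedance and symptoms as triggers expected to lead to such visits, so triggers and visits are kept apart.

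Under Sample size justification, the patient number is "intended to provide adequate power for the analysis of the primary objective". The rate behind it comes from 160 CRT-D patients: "Overall, 220 episodes occurred over 98 person-years (2.2 per person-year"). The components are "140 intra-thoracic impedance alerts", "34 episodes of atrial arrhythmia >12 hours in a single day", 6 further atrial episodes above 6 hours with a fast ventricular rate, and 40 shocks. The simulation takes 2.2 per person-year as its null rate, a 10% reduction and 20% uniform dropout. It reports 99.8% power with 100 patients per group.

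Four other places bear on the link from episode to visit:

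- Rationale for design says that "patients might not hear or respond to the audible impedance alert". It also says that shocks, alerts and symptoms usually send patients to the clinic.
- The text after Table 3 lets clinicians switch off the atrial and impedance alerts in defined circumstances.
- In Table 2 the row "Daily AT/AF Alert Burden" is set at 6 hours in both arms.
- The inclusion criteria admit ICD as well as CRT-D patients.

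**The concern.** The remote system is expected to let episodes be handled without a visit. The quantity it should change is the chance that an episode leads to a visit, and the planning model contains no such term. The model starts from an episode rate and calls it the rate for the primary objective.

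Power for a comparison of rates depends on the expected number of endpoint events. If the visit rate differs from the episode rate, the event count and the power differ with it. A reader then cannot tell what reduction in visits 200 patients can detect, and a non-significant result could be mistaken for evidence of no effect.

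**Working it through.** **Step 1: reproduce the planning rate.** 140 + 34 + 6 + 40 = 220 episodes. Person-time is 160 × 224 / 365.25 = 98.1 years, and 220 / 98 = 2.245, stated as 2.2. The simulated null rate is therefore the raw episode rate, and no conversion to visits lies between the two. Impedance alerts are 140 / 220 = 64% of the total.

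**Step 2: ask whether one episode equals one visit.**

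| Feature in the protocol article | Effect on the visit rate relative to 2.2 |
|---|---|
| Patients may miss or ignore the audible impedance alert (Rationale for design) | lowers |
| Clinicians may switch off impedance and atrial alerts (text after Table 3) | lowers |
| Visits for symptoms or system-integrity alerts belong to the endpoint (Objectives) but are not among the 220 | raises |
| The daily-burden atrial alert is set at 6 hours (Table 2), but 34 of the 220 episodes (15%) were counted at more than 12 hours | raises |
| Source patients all had CRT-D; the trial also takes ICD | direction not given |

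The article gives no size for any of these, so the net direction is unknown.

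**Step 3: power at the stated rate.** Inputs are 100 patients per arm, 16 months of follow-up, 20% uniform dropout and a two-sided 0.05 test. Mean follow-up is 0.9 × 16/12 = 1.2 years, which gives 120 person-years per arm. With control rate r and rate ratio RR, the expected counts are m0 = 120r and m1 = 120r × RR. For the large-sample comparison of two Poisson rates,

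d = (m0 − m1) / √(m0 + m1), and power = Φ(d − 1.96) + Φ(−d − 1.96).

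At r = 2.2 and RR = 0.90, m0 = 264, m1 = 237.6 and d = 26.4 / √501.6 = 1.179, so power is about 22%. A simulation of 20,000 trials under the same assumptions gave 22.1%. The stated 99.8% is not reproduced even on the episode scale. That is a separate arithmetic error and is not caused by the choice of event.

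**Step 4: power across control visit rates.** The article gives no visit rate. The rates below are assumptions, set at 25%, 50%, 75%, 100%, 125% and 150% of 2.2. The last column is the rate ratio at which power reaches 80%.

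| Control visits per person-year | Expected visits, control / remote at RR 0.90 | Power at RR 0.90 | RR detectable with 80% power |
|---|---|---|---|
| 0.55 | 66 / 59.4 | 9% | 0.56–0.57 |
| 1.1 | 132 / 118.8 | 13% | 0.68 |
| 1.65 | 198 / 178.2 | 18% | 0.74 |
| 2.2 | 264 / 237.6 | 22% | 0.77 |
| 2.75 | 330 / 297 | 26% | 0.79 |
| 3.3 | 396 / 356.4 | 30% | 0.81 |

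The first row shows a range because the rate-difference and log-rate-ratio forms differ slightly there. All figures assume Poisson variance. Repeat visits clustered in the same patients would lower power further.

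**The case against.** The strongest reply is that the episodes are not an unrelated quantity. The article treats alerts, arrhythmias and shocks as the triggers of the visits it counts, says that such events usually bring the patient in, and describes its data as extrapolated. An episode rate is then a reasonable starting point when visit data are lacking. This stands in part: the episode rate is a proxy, and the fault is that the one-to-one conversion is neither stated nor justified. "Usually" is not a proportion.

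Three stronger readings are tempting, and the document does not support them:

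- **A reader might infer that the visit rate must be below 2.2, because alerts can be missed.** Symptom and integrity visits and the 6-hour atrial alert push the other way.
- **A reader might infer that a ratio of 0.90 clashes with the statement that a high percentage of episodes may be managed remotely.** Planning on a smaller effect than the one hoped for is cautious, not contradictory.
- **A reader might infer that the effect itself is on the wrong scale.** If episodes occur equally often in both arms, and visits arise only from them, the visit rate ratio equals the ratio of visit probabilities. A ratio of 0.90 therefore has a clear meaning for visits; the baseline rate is what lacks support.

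The other mismatches are also limited. The 12-hour threshold concerns 34 of 220 episodes, and moving from CRT-D to a mixed device population is ordinary extrapolation.

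**Conclusion.** The concern holds as an unjustified proxy. The sample size section claims power for unplanned visits but uses a device-episode rate in its place, and the article itself gives reasons why the two differ in both directions. On the stated assumptions, moving the control visit rate between 0.55 and 3.3 per person-year moves power at a ratio of 0.90 between 9% and 30%, and the detectable ratio between about 0.56 and 0.81. The mismatch of events is certain. Its direction and size are not, because the visit rates are assumed.

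This point should not be credited with the fall from 99.8%. Power is already about 22% at an unchanged 2.2 per person-year. Correcting that arithmetic alone would still leave a power figure for episodes, and correcting the event alone would not repair the arithmetic.

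**What to change.** Restate the planning model in visits: control visit rate = episode rate × assumed probability that an episode leads to an unplanned visit, plus the rate of visits for symptoms and lead or device alerts. Give the source or assumption for each term. Count atrial episodes for planning on the same definition that the trial's alerts use; where the 12-hour and 6-hour figures differ, the two places must be reconciled.

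Replace the single power statement with the table above at N = 200, with control rates on both sides of 2.2, and note that overdispersion would reduce every entry.

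The pooled visit rate from patients already followed, tabulated without splitting by arm, can show which row applies. With equal person-time the pooled rate is r(1 + RR)/2, so at a ratio of 0.90 the control rate is the pooled rate divided by 0.95.

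The cost is a rewritten section and one pooled tabulation. The endpoint, the test and the number of patients stay the same. The downside is that the stated power becomes less favourable. The restatement makes the claim accurate but does not make the trial larger or show that 200 patients are enough.

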### Statistical methods

An intention-to-treat analysis will be performed on all randomized subjects and will serve as the primary analysis for all objectives in this study.

The primary and secondary hypotheses will be tested by using the Comparison of Incidence Rates (Large Sample) Test. A two-sided test and a significance level of α = 0.05 will be used.

Cost analysis will be carried out from the perspectives of the healthcare system and the patient. Consequently, the unit costs considered will be related to the public tariffs or to the patient's out-of-pocket expenses. The in-hospital resources related to the introduction and utilization of CareLink will also be evaluated.

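### The stated 99.8% power for a rate ratio of 0.90 does not follow from the plan's own inputs, which give about 22%

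*Protocol article*

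**What the plan says.** All inputs are printed in the protocol article.

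- **Rate and effect** (Sample size justification): "the incidence density used as a null hypothesis was 2.2 per person-year; this rate is expected to decrease by 10% in the study arm". The rate comes from a CRT-D cohort in which "220 episodes occurred over 98 person-years (2.2 per person-year").
- **Dropout** (same section): "it was assumed that 20% of patients would drop out uniformly over the follow-up period".
- **Sample size and power** (same section): "A sample size of 100 subjects per group would allow a power of 99.8" per cent, with a 95% confidence interval of 96.0 to 100.0, for a rate ratio of 0.90 at a type I error of 0.05.
- **Test** (Statistical methods): the primary and secondary hypotheses are "tested by using the Comparison of Incidence Rates (Large Sample) Test". "A two-sided test and a significance level of α = 0.05 will be used".
- **Allocation and follow-up** (Design; Procedures): one-to-one randomization, and 16 months per patient.

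**The concern.** A 10% difference in rates is small compared with the sampling error of about 250 events per arm. Power close to 100% is therefore implausible on sight, and the inputs are complete enough to check it.

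The power figure is the only support given for the sample size. If 99.8% were right, a non-significant primary result would be strong evidence against a 10% reduction in unplanned visits. If the true power is about 22%, a non-significant result is expected about 78 times in 100 even when that reduction is real, and it says little either way.

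**Working it through.** **Inputs.** 100 per arm; 16/12 years per patient; 20% dropout, uniform, so a dropout contributes half the period on average; control rate 2.2; remote rate 2.2 × 0.90 = 1.98; two-sided alpha 0.05. Counts are taken as Poisson, because the document gives no figure for between-patient variation.

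**The rate reproduces.** 140 + 34 + 6 + 40 = 220 episodes; 160 × 224 / 365.25 = 98.1 person-years; 220 / 98 = 2.24, printed as 2.2.

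**The power does not.**

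1. Person-years per arm = 100 × (16/12) × (0.8 + 0.2 × 0.5) = 120.
2. Expected events: 2.2 × 120 = 264 and 1.98 × 120 = 237.6.
3. Rate difference = 0.22. SE = √(2.2/120 + 1.98/120) = 0.1866. With equal person-years the pooled SE has the same value.
4. Power = Φ(0.22/0.1866 − 1.96) = Φ(−0.78) = 21.7%.
5. Log-ratio form: SE = √(1/264 + 1/237.6) = 0.0894; |ln 0.90| = 0.1054; z = 1.18; power 21.7%, or 21.8% with the opposite tail included.
6. A simulation of 20,000 trials with uniform dropout and the pooled rate test gave 21.8%, with a type I error of 5.0%.

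As a simple cross-check, significance needs an observed rate ratio below about exp(−1.96 × 0.0894) = 0.84. A trial that observed exactly 0.90 would not be significant.

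**Other readings of the inputs** (two-sided unless stated):

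| Reading | Power |
|---|---|
| Dropouts contribute no time | 19.8% |
| As stated | 21.7% |
| No dropout | 23.7% |
| Common close, mean 22 months, same dropout pattern (165 person-years per arm) | 28% |
| Common close, mean 22 months, no dropout | 31% |
| As stated, one-sided | 32.1% |
| No dropout, one-sided | 34.4% |
| One-sample test against a fixed 2.2, 120 person-years | 36.2% |
| One-sample test, 240 person-years | 63.9% |
| 200 per arm, no dropout, one-sample, one-sided | 79.4% |

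The last three readings already depart from the planned two-arm test.

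**What the design does deliver.** With 120 person-years per arm, power is 80% at a rate ratio of about 0.77, 90% at about 0.74 and 99.8% at about 0.62.

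**What 0.90 would need.** Person-years per arm = (1.96 + z)² × (2.2 + 1.98) / 0.22², where z is the normal quantile of the power. For 80% this is 678, or 678 / 1.2 = 565 patients per arm. For 99.8% it is about 2,022, or about 1,685 patients per arm.

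**The case against.** **The power was simulated and the code is not shown.** True, so the cause of the discrepancy cannot be identified. But the hypotheses of the simulation are listed, and a simulation run under them agrees with the closed formula. Unseen code could explain how 99.8% arose; it could not make that figure follow from the printed inputs. The effect is printed twice, as a 10% decrease and as a ratio of 0.90, so a single slip in the effect size is not an easy explanation.

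**Follow-up may be longer than 16 months.** The Summary section puts the end of follow-up 16 months after the last enrollment, with enrollment from May 2008 to May 2009. If every patient were followed to that close, mean follow-up would be about 22 months under uniform accrual, and power 28–31%. Procedures supports 16 months per patient, so 22% is the better reading, but the range should be known. It does not alter the conclusion.

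**The true effect may be larger than 10%.** It may, and the trial has reasonable power for a reduction of about 23%. That is not the effect the section claims to cover.

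**Overdispersion.** A reader might infer that clustering of events within patients pushes power below 22%. That holds only for a test that adjusts for clustering. The article names the large-sample rate comparison and states no variance adjustment, and that test would reject too often. With an assumed gamma frailty of variance 1, it rejects 39% of the time at a ratio of 0.90, but also 32% of the time under no effect. The consequence there is an inflated type I error, and it does not rescue 99.8% at the stated alpha of 0.05.

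**The interval of 96.0 to 100.0.** A reader might try to show from it that the simulation was faulty, by working back to a number of runs. The article does not say how the interval was formed, so that argument rests on an assumption and is not made here.

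**Conclusion.** The stated power is wrong as written. Under the plan's own inputs it is about 22%, against 99.8% stated. Alternative follow-up, dropout and sidedness assumptions for the two-arm test at 100 per arm move it between about 20% and 34%. Even the most generous departure tried, with twice the patients, no dropout and a one-sided one-sample test, stops at 79%.

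The 22% rests on 16 months per patient, Poisson counts without between-patient variation, and a control rate of 2.2. That rate counts alerts, arrhythmia episodes and shocks in an earlier cohort, whereas the primary endpoint is unplanned visits. The power is therefore conditional on visits occurring at that rate.

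A reader might infer that the trial cannot detect a 10% reduction, or that 200 patients is an indefensible number. The documents support neither. The trial has roughly a one-in-five chance of detecting a ratio of 0.90 and is adequately powered for a ratio of about 0.77 under the same assumptions. What fails is the claim attached to the sample size.

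**What to change.** Keep N = 200 and replace the power sentence in Sample size justification with:

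> Assuming a control rate of 2.2 events per person-year, 16 months of follow-up per patient, 20% uniform dropout and Poisson counts without between-patient variation, 100 patients per arm (about 120 person-years per arm) give about 22% power for a rate ratio of 0.90 and about 80% power for a rate ratio of about 0.77 (two-sided alpha 0.05).

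Remove the 96.0 to 100.0 interval, since it belongs to the unsupported figure. Add that the primary result will be read from the rate ratio with its 95% confidence interval, and that a non-significant result will not exclude a 10% reduction. Any remark on overdispersion should be limited to a test that adjusts for it.

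The cost is one rewritten paragraph and a much less favourable stated power. No patients, visits or procedures change.

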## Discussion

### Rationale for objectives

The CareLink system performs full interrogation and transmission of ICD data, and available information is no different from that retrieved during an in-office visit. The main advantage lies in the possibility of early reaction to patient symptoms and device alerts without the patient having to come to the hospital for either scheduled or unscheduled examinations.

As suggested [10,15], adoption of the CareLink system should enable cardiac or ICD-related episodes to be successfully managed through remote data review and telephone follow-up, without requiring additional in-hospital visits. This will be ascertained by measuring the reduction in the rate of unplanned in-hospital visits (primary objective). Moreover, it is hypothesized that this reduction will concern both visits related to the worsening of HF and those that are not HF-related, which in current clinical practice are managed by the heart failure specialist and the electrophysiologist, respectively. More generally, it is supposed that the rate and the costs of total healthcare utilizations for cardiac or ICD-related events will decrease; this will be tested as a secondary objective.

### Rationale for design

Currently, outpatient follow-up examinations of ICD patients are scheduled at regular 3- to 6-month intervals [8,9]. In the present study, we will compare a standard arm undergoing 4 in-office examinations per year with a remote arm in which 2 of the 4 examinations are replaced by remote interrogations, as previously proposed [16,17].

Acute events, such as ICD shocks, alerts or symptoms that usually prompt the subject to seek urgent attention at the clinic, will be managed via CareLink and telephone follow-up in the remote arm. Indeed, it has been recently shown that a considerable portion of post-shock interrogations do not involve reprogramming of the ICD and may therefore be performed remotely [10,15].

The audible alert feature has been shown to facilitate the early discovery of serious ICD complications [7], and improved alert algorithms have recently been implemented to detect lead failures promptly [6]. Similarly, in view of the high incidence of atrial fibrillation in HF [18] and the consequent increased risk of decompensation, stroke and inappropriate shocks, the advanced ICD capabilities for detecting atrial arrhythmias have the potential to play a growing role in patient monitoring [5]. By providing remote notification and access to details of the occurrence and duration of atrial fibrillation and ventricular response, CareLink will facilitate the management of therapies for rhythm or rate control and the prompt administration of anticoagulants for stroke prevention.

Continuous intra-thoracic impedance monitoring in modern ICD is intended to detect HF decompensation promptly, thereby permitting early therapeutic intervention [4]. Decreased intra-thoracic impedance has been shown to reliably identify acute HF, with low rates of undetected events [19], and to be associated with an increased risk of HF hospitalization [20]. As recently shown [15], a high percentage of episodes may be successfully and promptly managed through CareLink without requiring additional in-hospital visits, by means of remote data review and assessment of symptom status and therapy compliance by phone. Moreover, patients might not hear or respond to the audible impedance alert, as recently reported [21]. Thus, automated telemetric transmission of alerts to the physician may shorten the delay between alert and therapy initiation, further improving the clinical outcome.

Other trials have used a control arm blinded to device data [22], in order to test the clinical value of diagnostic features. By contrast, in the present study all alerts will be turned on for audible notification in the standard arm and the diagnostics will be open for in-office review. This will enable the benefits associated to remote notification and access to ICD data to be specifically assessed in addition to the diagnostic and alerting capabilities of modern ICD.

Another trial is currently investigating the CareLink system in pacemaker patients [23]. The present study on ICD/CRT-D patients, however, will focus on a sicker population with more complex devices. This is the setting in which remote monitoring is presumed to offer the greatest benefits.

In the hypothesis of a more stable clinical status of the patient and a reduced need to adjust ICD parameters 6 months after implantation [10], stratifying patient randomization on the basis of time since implantation will limit a potential bias.

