***Intra-thoracic Impedance Monitoring (OptiVol Alert)***		

*OptiVol Alert – Device*	Off	On

*OptiVol Alert – Monitor*	On	Off

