***Number of Shocks Delivered during an Episode***		

*Alert Enable – Device*	Off	Off

*Alert Enable – Monitor*	On	Off

*- Threshold Number of Shocks*	1	-

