***VF Detection/Therapy Off***		

*Alert Enable – Device*	On-High	On-High

*Alert Enable – Monitor*	On	Off

* For systems with an LV lead; ** For systems with dual-coil leads

In summary, all alerts regarding clinical management (intra-thoracic impedance for fluid accumulation monitoring, atrial arrhythmias, ICD shocks delivered) will be turned on for wireless notification through the CareLink in the remote arm, while no audible alerts will be used. In the standard arm these alerts will be turned on for audible notification only.

All lead and device integrity alerts will be turned on for both wireless and audible notification in the remote arm, and for only audible notification in the standard arm.

In the standard arm, audible alerts for intra-thoracic impedance monitoring will be programmed to sound at a different time of the day from alerts for other causes, in order to distinguish them.

Clinicians are allowed to turn off the alert for atrial arrhythmias, if they are no longer attempting to control the subject's atrial rhythm. Similarly, they can turn off the alert for intra-thoracic impedance when recurrent inappropriate detections of fluid accumulation are documented.

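### For the clinical alerts CareLink replaces the audible alert, so the claim to assess remote notification in addition to device alerting is unsupported; the comparison of strategies stands

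*Protocol article*

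**What the plan says.** The protocol article, Discussion, Rationale for design, contrasts this trial with trials whose control arm was blinded to device data. Because the standard arm here has audible alerts and open diagnostics, it says, the design allows "benefits associated to remote notification and access to ICD data to be specifically assessed in addition to the diagnostic and alerting capabilities" that current devices have.

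The summary under Device programming describes the two arms. Clinical management alerts "will be turned on for wireless notification through the CareLink in the remote arm, while no audible alerts will be used". The next sentence reads: "In the standard arm these alerts will be turned on for audible notification only". The integrity alerts are handled differently: "All lead and device integrity alerts will be turned on for both wireless and audible notification in the remote arm", and audibly only in the standard arm.

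Under Objectives, the primary endpoint is the rate of unplanned cardiac or device-related in-hospital visits. The events expected to prompt them include system-integrity and arrhythmia alerts, "decrease in intra-thoracic impedance signifying possible fluid accumulation, and patients' symptoms". The Abstract and the Rationale for design also describe alerts as a reason why patients come to hospital unscheduled.

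**The concern.** Assessing remote notification in addition to the device's own alerting would require the same audible alerting in both arms, with CareLink added in one. For most clinical alerts the two arms differ in two respects at once: the clinic is notified remotely, and the patient no longer hears the device. The second difference acts directly on the endpoint, because a sounding device is one of the things that bring a patient in.

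What is at stake is the reading of a positive primary result. A lower visit rate would show that one strategy leads to fewer unplanned visits than the other. It would not show how much is due to remote notification and data access, which is what the Discussion says the design can assess specifically.

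**Working it through.** **Programming by alert class** (Device programming, Tables 2 and 3)

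| Alert class | Audible, remote arm | Audible, standard arm | Wireless, remote arm | Contrast |
|---|---|---|---|---|
| Impedance (row "OptiVol Alert – Device") | Off | On | On | replacement |
| AT/AF burden (row "AT/AF Daily Burden Alert Enable – Device") and ventricular rate during AT/AF | Off | On | On | replacement |
| All therapies in a zone exhausted | Off | On | On | replacement |
| Shocks (block "Number of Shocks Delivered during an Episode") | Off | Off | On | wireless added, no audible alert in either arm |
| Lead impedance, battery, charge time, VF detection/therapy off | On-High | On-High | On | add-on |

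Wireless notification is off throughout the standard arm. The contrast described in the Discussion, wireless on top of the same audible alert, exists only in the last row.

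The shock row also conflicts with the text. The Device programming summary counts shocks among the clinical alerts that are audible in the standard arm, and the Discussion says all alerts are audible there. Table 2 has the shock device alert Off in that arm.

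**Planning data** (Sample size justification)

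The components add up to the stated total: 140 + 34 + 6 + 40 = 220 episodes. The rate is 220/98 = 2.24 per person-year, given as 2.2.

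Episodes of types audible in one arm only: a = 140 + 34 + 6 = 180. Shocks: s = 40. Share: 180/220 = 81.8%.

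The planned effect is a 10% reduction, or 0.10 × 220 = 22 episodes.

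**Illustration**

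Let q be the share of audible alerts that prompt a visit in the standard arm, and f the fraction of those visits lost in the remote arm only because the patient hears nothing. Assume that every shock prompts a visit in both arms. The documents give neither q nor f.

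- Standard-arm visits: q·a + s
- Remote-arm visits: q·(1 − f)·a + s
- Loss that gives a rate ratio of 0.90: f = 0.10 × (q·a + s)/(q·a)

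| q (assumed) | Calculation | f needed |
|---|---|---|
| 100% | 0.10 × 220/180 | 12.2% |
| 75% | 0.10 × 175/135 | 13.0% |
| 50% | 0.10 × 130/90 | 14.4% |
| 25% | 0.10 × 85/45 | 18.9% |

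The 82% share is approximate for three reasons. The planning count used atrial arrhythmia above 12 hours, whereas Table 2 programs a 6-hour burden. The planning cohort had CRT-D only, whereas the trial also enrols ICD patients. Clinicians may switch off the AT/AF and impedance alerts in defined circumstances. The planning list has no separate count for therapies-exhausted alerts.

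**The case against.** The strongest reply is that the trial tests a strategy and says so. The Abstract, the Objectives and the Summary all compare remote management, or use of CareLink, with standard care. Randomisation identifies that contrast, and the programming is stated openly. This stands. A reader might infer that the primary comparison itself is confounded or invalid; the documents do not support that.

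It can also be said that the disputed sentence describes the comparator: an active control with audible alerts, as opposed to a blinded one. That is a fair reading of its context. The sentence nevertheless goes on to say that the benefits of remote notification and access are specifically assessed, and for the replaced alerts they are not separable.

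A third reply is that no alert is lost. Under Management strategies the clinic receives it and the clinician is required to act, so a visit avoided after remote review is the mechanism under test. The Rationale for design adds that patients may not hear or respond to an audible alert. This also stands. A reader might infer that silence alone would explain a lower rate. The documents do not show that; they leave it as one component that the visit count cannot separate.

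Finally, the protocol has other measures that bear on benefit: time to clinical decision, the Clinical Composite Score, and the classification of visits as necessary or unnecessary. They help interpretation. However, the first two are not the primary endpoint, and the third judges only visits that took place.

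**Conclusion.** The point holds as a limit on what may be concluded. For impedance, AT/AF and therapies-exhausted alerts the trial compares CareLink notification in place of an audible alert with an audible alert without CareLink. Only the lead and device integrity alerts give an add-on contrast. The statement that remote notification is specifically assessed on top of device alerting is therefore unsupported for the classes that make up about 82% of the planning episodes. The primary test and the comparison of strategies are unaffected.

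The programming conclusion rests on Tables 2 and 3 and needs no assumption. The 12% to 19% range is illustrative only. It assumes that between 100% and 25% of audible alerts prompt a visit and that every shock does, and it takes over the approximate 82% share. It shows that a modest loss of audibly prompted visits could match the planned 10% reduction, not that such a loss will occur.

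It might also be inferred that an effect should be credited to remote notification only if it appears among integrity alerts, shocks or symptoms. That rule would be unsound. The trigger of a visit arises after randomisation and depends on the arm: the same impedance crossing may be recorded as an audible alert in one arm and as a clinic call or symptoms in the other.

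**What to change.** Leave the programming and the primary test as they are.

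1. Restate the sentence in the Rationale for design, and the conclusion to be drawn from the primary result, as a comparison of two strategies: CareLink notification replacing audible clinical alerts, versus audible alerts without CareLink.
2. Record the trigger at each unplanned visit and report visits by arm and trigger: audible clinical alert (including therapies exhausted), clinic-initiated after a wireless alert, lead or device integrity alert, shock, symptoms. Keep this descriptive, with no formal attribution rule. The trigger has to be taken at the visit itself, because Table 1 collects symptoms at 4 and 12 months in the standard arm only.
3. Reconcile the Discussion (all alerts audible in the standard arm) and the Device programming summary (shocks included) with Table 2, where the shock device alert is Off in that arm.

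The cost is a change of wording, one extra item per unplanned visit and one table. The downside is a narrower claim and sparse counts in some trigger classes, probably the integrity alerts above all.
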